### 2.6 Blinding

During the participant recruitment phase, potential participants are informed that the study is focused on evaluating neural responses to tDCS. However, no specific information has been provided about the existence of sham tDCS or the distinctions between these two types of stimulation. To preserve the integrity of blinding, the tDCS device’s screen remains concealed from participants, and the allocation of participants into the experimental or sham group is undisclosed to both the participants and the researchers. Furthermore, the application of tDCS is carried out by a technician who is unaware of the research objectives. In the sham tDCS condition, there is a 30-second ramp-up to 3 mA, immediately followed by a 30-second ramp-down to zero intensity. This design is intended to create a sensation similar to that of a real stimulation without actual delivery. To assess the effectiveness of blinding, participants will be queried at the study’s conclusion to make an informed guess about whether they received real or sham stimulation.

### 2.7 Randomization

To ensure unbiased participant allocation, we will use an online block randomization tool (https://www.sealedenvelope.com/simple-randomiser/v1/lists) with a block size of six, dividing participants into two treatment groups. The allocation process will be concealed using unique codes, which will be sealed within opaque envelopes. These envelopes will be prepared in advance by a research assistant who is not directly involved in this study. The intervention will be administered by separate investigators who are not linked to the assessment of the outcome measures. Additionally, the experimenter responsible for conducting the outcome measures will remain blinded to the tDCS conditions.

### 2.8 Intervention

tDCS will be administered using the DC-Stimulator Plus device (Neuroconn GmbH, Germany). A constant current of 3 mA will be applied for a duration of 20 minutes, with 30-second ramp-up and ramp-down periods, delivered between two sponge electrodes, each measuring 7 x 5 cm^2^, soaked in saline solution. The anode electrode will be positioned over the left DLPFC (F3 based on the 10–20 EEG system) and the cathode electrode will be situated over the DLPFC (F4). This bilateral electrode arrangement is chosen to primarily increase excitability over the left DLPFC in line with previous tDCS studies in the SCZ [38, 39]. The placement of the return electrode (here cathodal) has been different (e.g., right DLPFC, orbitofrontal cortex, temporoparietal junction) in previous tDCS studies but was mostly on the right hemisphere [38]. We place the cathode over the right DLPFC as the DLPFC is the primary target here and of interest for BOLD response following tDCS. In the sham control condition, the same electrode positions and ramping periods will be employed, but a 3-mA current will only be delivered during the initial minute of the 20-minute session to induce a temporary tingling sensation on the scalp, ensuring participant blinding. Participants will be informed of the possibility of experiencing mild tingling or itching sensations resulting from the electrodes’ contact with the scalp. To prevent skin irritation due to the 3-mA current and also prevent unblinding, an anesthetic cream will be applied under the electrodes and over the scalp. Following each active or sham session, participants will complete a checklist to record any adverse effects. The electrical field induced by this protocol is modeled in Fig 3 using the SimNIBS software [40]. The stimulation will be delivered online, that is, during cognitive task performance. After the stimulation and at the end of the experiment, a side effect survey on tDCS common side effects (e.g., itching, tingling, burning, pain sensations) will be conducted. In the event of a significant increase in the risk of serious adverse events, such as severe itching or redness at the electrode sites, or if safety concerns arise from the Research Ethics Committee of Iran University of Medical Sciences, the investigators will have the authority to halt the trial.

**Fig 3 pone.0306422.g003:**
[figure not shown]
a) Modeling of induced Electrical field of 3 mA bilateral frontal montage with anode in left DLPFC and cathode in right DLPFC (red rectangle: anode, blue rectangle: cathode), b) Illustration of the 3-back test and instructions to the participants as an example.

### 2.9 Magnetic resonance imaging

MRI assessments will be performed using a Siemens MAGNETOM Prisma 3 Tesla scanner, equipped with a 64-channel head coil. These assessments will take place both before and immediately after the intervention. Each MRI session will encompass whole-brain structural images with T1-weighted acquisition and rs-fMRI scans. Each MRI session will include the acquisition of whole-brain structural images and resting-state fMRI (rs-fMRI) scans. The T1-weighted images will be acquired over five minutes using MPRAGE pulse sequences with parameters set at a TR of 1800 ms, TE of 3.53 ms, a voxel size of 1 × 1 × 1 mm^3^, and a flip angle of 7°. Additionally, rs-fMRI will be conducted for 15 minutes using an EPI sequence with a TR of 2000 ms, TE of 30 ms, a voxel size of 3 × 3 × 3 mm^3^, and a flip angle of 90°.

### 2.10 Outcome measures and assessments

#### 2.10.1 Working memory task

To assess working memory performance, we will employ the N-back task, a widely recognized ’executive’ assessment for working memory (WM) (Fig 3) related to the prefrontal cortex (PFC) [41]. This task requires continuous monitoring and updating of the remembered information. Participants will be presented with a sequence of numbers one at a time and are instructed to indicate when the current number matches the one presented n” steps earlier in the sequence. The working memory demand increases with higher ’n-back’ levels. In our study, participants will engage in both 1-back and 3-back conditions in line with previous works [42], once prior to the intervention (tDCS/fMRI) session for baseline assessment and once during the online stimulation. In the 1-back task, participants identify when the current number stimulus matched the one immediately preceding it, placing minimal demand on the working memory. In the more challenging 3-back, participants must recognize when the current stimulus matches the one shown three steps back, necessitating the maintenance and manipulation of information in working memory.

The N-back test will be implemented using MATLAB (MathWorks, Inc., 2019) and the PsychToolbox library. The experiment comprised 120 trials, with each stimulus (a digit between 0–9) displayed for 0.5 seconds followed by an inter-trial interval (ITI) that was dependent on the N-back level, calculated as 2 + 0.25 * (N_back_-1) seconds. Participants were prompted to respond by pressing the ’Space’ key for N-back instances. During the training stage, a shorter version with visual feedback will be applied, where the screen turns red when the wrong button is pressed, and green for the correct response. Outcome measures include accuracy, reaction time for correct responses (ms), and d-prime—a bias-free measure of observer sensitivity [43] considering both correct hits and false alarms. D-prime is calculated as

d′=z(Hitrate)−z(Falsealarmrate)

Although our study design did not initially include direct measures of response bias through differentiated response buttons, we recognize its importance. We propose evaluating the response bias using the criterion C = −0.5[z(hit rate)+z(false alarm rate)], as suggested by Huh et al. (2006) [44], to infer participants’ response tendencies from our data, despite the constraints of our data collection protocol. A comparison of 1-back and 3-back performances will provide a robust characterization of working memory abilities. Before the start of the baseline block, participants will perform continuous training on both 1 and 3-back tasks until they reach a stable level of performance (>70% accuracy).

#### 2.10.2 Primary outcomes

The primary outcome measures are:

change in the d’ index of the n-back task from baseline to the online stimulation session, which will be assessed in both the sham and active tDCS groups and 24 hr after the interventionChange in the accuracy of the n-back task from baseline to the online stimulation session and 24 hr after the interventionChange in the reaction time of correct responses of the n-back task from baseline to the online stimulation session and 24 hr after the interventionChanges in rs-fMRI functional connectivity by measuring correlations in spontaneous BOLD signal fluctuations between cortical and subcortical regions of interest (ROIs) before and after tDCS administrationChanges in rs-fMRI functional connectivity by examining correlations between spontaneous BOLD signal fluctuations in the stimulated cortical area under the anode/cathode electrodes and the entire brain, both before and after tDCS.

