### 2.5 Sample size estimation

The sample size is determined a priori through power analyses via G*Power 3.1 [35], indicating that a minimum of 42 subjects is required to achieve 95% power at a significance level of 0.05 for the primary statistical test of a mixed-model ANOVA design, with two groups, 3 measurements of working memory performance (baseline, during stimulation and 24 hours after stimulation), given a medium effect size (f = 0.25, equivalent to η^p2^ = 0.10 which is used in ANOVA models). This effect size is recommended in NIBS studies [36]. To account for a potential dropout rate during the study, we propose including an additional 3 participants in each group (i.e., 6), totaling 48, which is more than the majority of published studies in terms of sample size and retention rate [37, 38].

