### 2.12 Statistical methods

To assess the efficacy of the tDCS intervention, we will conduct a mixed model analysis of variance (mixed-ANOVA) on the n-back task indices, including d-prime, reaction time, and accuracy with time (before and after tDCS) as the within-subject factor and group (active tDCS and sham tDCS) as the between-group factor and their interaction. The group × time interaction effect and the main effect of group and time will be explored to see if changes in working memory performance and brain activation (two key dependent variables) are influenced by the type of stimulation (group factor) and time (before vs during stimulation). The normality and homogeneity of data distribution, and variance will be confirmed by Shapiro-Wilk and Levin tests, respectively. Mauchly’s test will also be used to evaluate the sphericity of the data before performing the ANOVA. In case the assumption of sphericity was violated, the degrees of freedom were corrected using Greenhouse-Geisser estimates of sphericity. To investigate the associations between changes in brain activity/connectivity and task performance changes, we will employ the Pearson correlation test. This test will help identify potential relationships between changes in brain activity and task performance, providing valuable insights into the neural mechanisms underlying our observations. All statistical analyses will be conducted using R [45].

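### Five unranked primary outcomes, a different primary set in the abstract, and a sample size built on one unnamed primary test at 0.05

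*Protocol article*

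**What the plan says.** - **Primary outcomes (Section 2.10.2).** "The primary outcome measures are" introduces five items: change in d-prime, in accuracy and in reaction time, each tied to online stimulation and to 24 hours; ROI-to-ROI connectivity before and after stimulation; and connectivity of the stimulated area with the whole brain before and after stimulation. None is ranked first.
- **Abstract, Methods.** The primary outcome is given as change in brain activation plus working memory, the latter specified as accuracy and reaction time. D-prime is not mentioned, and connectivity is not named.
- **Sample size (Section 2.5).** At least 42 participants give "95% power at a significance level of 0.05 for the primary statistical test of a mixed-model ANOVA design", with "3 measurements of working memory performance (baseline, during stimulation and 24 hours after stimulation", "given a medium effect size (f = 0.25". The index and the load are not named.
- **Task (Section 2.10.1).** "participants will engage in both 1-back and 3-back conditions", once at baseline and once during stimulation. No 24-hour administration is scheduled there.
- **Analysis (Section 2.12).** A "mixed model analysis of variance (mixed-ANOVA) on the n-back task indices, including d-prime, reaction time, and accuracy". The factors are group and time; load is not a factor. Time is described first as before and after stimulation, then as before versus during. The interaction and both main effects are to be examined, and working memory performance and brain activation are called the two key dependent variables.

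**The concern.** The choice of primary outcome belongs in the protocol, and here the sections make it differently. The abstract, Section 2.10.2 and Section 2.12 each describe another primary set, and Section 2.5 refers to a single test that none of them identifies. Two things follow.

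First, if any one of several primaries can support the claim, a p-value below 0.05 on one of them is weaker evidence than the sample size section implies. The abstract says positive results could prompt rapid, wider testing, but the document does not define a positive result. Faster but less accurate responding, for example, would move two primaries in opposite directions.

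Second, even one chosen index is not fully specified. Two loads are measured, and the model neither separates them nor says how they are combined. Whether the 24-hour point belongs to the primary contrast depends on which section is read. The d-prime formula in Section 2.10.1 also has no finite value when a hit or false-alarm rate is exactly 0 or 1.

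**Working it through.** **1. Reproduce the plan's sample size.** Inputs from Section 2.5: f = 0.25, two groups (k = 2), three measurements (m = 3), alpha 0.05, N = 42. Assumed, because not stated: correlation between measurements rho = 0.5, and sphericity. For the group-by-time interaction:

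lambda = f² × N × m / (1 − rho) = 0.0625 × 42 × 3 / 0.5 = 15.75

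df1 = (k − 1)(m − 1) = 2; df2 = (N − k)(m − 1) = 80

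The noncentral F distribution gives power of 94.6% at N = 42. It passes 95% at N = 43, or 44 with equal arms. The stated 42 is therefore reproduced to within two participants, as the size for one interaction test on one index. Under the same assumptions the between-group main effect has 49.1% power at N = 42, so that is not the effect the trial was sized on.

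**2. Count the tests.** Only the three n-back outcomes have loads and a 24-hour point. The two connectivity outcomes have one before/after contrast each.

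- One test per listed outcome: 5.
- Loads tested separately: 3 × 2 + 2 = 8.
- Loads and both post-baseline times tested separately: 3 × 2 × 2 + 2 = 14.

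**3. Family-wise error** if each test is at 0.05 and any one suffices. For independent tests it is 1 − 0.95^K:

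- K = 5: 1 − 0.95^5 = 22.6%
- K = 8: 1 − 0.95^8 = 33.7%
- K = 14: 1 − 0.95^14 = 51.2%

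For equally correlated two-sided normal tests (simulation, 400,000 draws; the correlations are assumed, as the document gives none):

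| Tests | r = 0.3 | r = 0.5 | r = 0.7 | r = 0.9 |
|---|---|---|---|---|
| 5 | 20.8% | 18.3% | 14.8% | 10.2% |
| 14 | 44.0% | 34.9% | 24.8% | 14.1% |

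In a block structure (d-prime with accuracy 0.7 to 0.9, reaction time with either 0.2 to 0.5, the connectivity pair 0.3 to 0.7, no correlation between the blocks), five tests give about 18% to 21%. Fourteen give about 36% to 45%, with loads correlated 0.3 to 0.5 and times 0.5 to 0.7.

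**4. Power of the two candidate primary contrasts** (same formula, f = 0.25, rho = 0.5, alpha 0.05):

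- Three measurements: 94.6% at N = 42; at N = 48, lambda = 18.0 and power is 97.0%.
- Baseline to online only (m = 2): lambda = 0.0625 × 42 × 2 / 0.5 = 10.5 on 1 and 40 df, power 88.5%; at N = 48, lambda = 12.0 and power is 92.4%. Reaching 95% needs N = 54.

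**5. Keeping five primaries with a Bonferroni split** (0.05 / 5 = 0.01 each): the three-measurement test has about 83% power at N = 42 and 89% at N = 48, and needs N = 58 for 95%.

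**The case against.** The strongest defence is that this is a condensed article, and multiplicity adjustment, a success rule and scoring details may sit in an analysis plan that is not shown. That stands: the absence of an adjustment formula is not the point here. It does not answer the conflict over what the primary outcome is, because no analysis plan can adjust coherently for a family that the protocol defines in several ways.

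It is also fair that this is a single-session mechanistic study meant to inform larger trials. That lowers the stakes, but the fix costs little. Section 2.10.1 and the subsequent text on response bias give a purpose for using two loads, namely to compare them, but do not say which one decides.

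Some stronger readings are tempting and are not supported:

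- *The false-positive risk is at least 15%.* This is not a floor. D-prime and accuracy are scored from the same responses, so high correlation is plausible, and at r = 0.9 five tests give about 10%.
- *The risk is about 50%.* That needs 14 independent tests. The 24-hour point is missing from Sections 2.10.1 and 2.12, and a three-level omnibus time test gives one interaction test per index and load, hence 8 tests rather than 14.
- *Every primary has two loads and two times.* The connectivity outcomes have neither.
- *The plan tests every primary at 0.05.* This is inferred; 0.05 appears only in Section 2.5.
- *The 1-back will be near ceiling.* The protocol says only that its demand is minimal. Participants are selected for cognitive impairment and trained to just above 70% accuracy.
- *Naming one primary costs no power.* This depends on the contrast, as step 4 of the working shows.

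**Conclusion.** The point holds as a defect in how the protocol fixes its primary outcome. Five co-equal outcomes, a different set in the abstract, an unnamed index behind the sample size, an undecided load and a 24-hour assessment present in some sections and absent in others leave it open which result decides the trial.

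The size is conditional on testing each primary at 0.05 with any one sufficient. For one test per outcome, family-wise error is 22.6% under independence and about 10% to 21% for correlations of 0.9 to 0.3. The 34% (8 tests) and 51% (14 tests) are upper values under independence, not expected ones. ROI-pair or voxel-wise testing could add to these figures, but the document does not say how many such tests there would be.

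**What to change.** Before unblinding:

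1. Name one primary index, one load and one contrast, with the group-by-time interaction as the deciding test at two-sided 0.05. 3-back d-prime is a reasonable choice, since Section 2.10.1 describes the 3-back as the more demanding condition and d-prime as free of bias. The sponsor may prefer another, but it must be one.
2. Make the other n-back indices and the 1-back secondary, under Holm or fixed-sequence control. Name one connectivity measure as the key imaging secondary and label the remaining connectivity analyses exploratory.
3. Reconcile the abstract and Sections 2.5, 2.10.1, 2.10.2 and 2.12 on the primary set, the load and the 24-hour assessment.
4. State a standard correction for d-prime when a rate is 0 or 1.
5. Restate power for the chosen contrast. If it is baseline to online, the figures are 88.5% at N = 42 and 92.4% at N = 48, so the stated 95% no longer applies.

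The cost is wording in the protocol and related documents. Four outcomes lose primary status, and a two-measurement primary means accepting lower power or recruiting more participants (54 analysed for 95%, under the same assumptions). Keeping five primaries at 0.01 each would need 58.

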#### 2.10.3 Exploratory outcomes

We will perform exploratory analyses to investigate the correlations between changes in physiology and changes in cognitive performance before and after tDCS. This approach allows us to assess the intricate relationship between brain function and behavior. Furthermore, our objective is to identify potential predictors of variations in working memory task performance and individual responses to the intervention, taking into account a range of clinical and biological measures. In addition, we will incorporate the induced electric field (E-field) in the prefrontal area for each participant. This E-field is determined through an analysis of the computational finite-element model with simNIBS software and is considered as a potential predictor of how the brain responds to tDCS.

### 2.11 Data management

The research team consists of the principal investigator, a trained psychiatrist, professional researchers, and research assistants. Monthly meetings are held to maintain project administration consistency, address critical matters, and monitor trial progress. The psychiatrist directly communicates with the patients. Two professionally trained researchers are tasked with collecting and inputting verified data, all while being supervised by [name].

### 2.12 Statistical methods

To assess the efficacy of the tDCS intervention, we will conduct a mixed model analysis of variance (mixed-ANOVA) on the n-back task indices, including d-prime, reaction time, and accuracy with time (before and after tDCS) as the within-subject factor and group (active tDCS and sham tDCS) as the between-group factor and their interaction. The group × time interaction effect and the main effect of group and time will be explored to see if changes in working memory performance and brain activation (two key dependent variables) are influenced by the type of stimulation (group factor) and time (before vs during stimulation). The normality and homogeneity of data distribution, and variance will be confirmed by Shapiro-Wilk and Levin tests, respectively. Mauchly’s test will also be used to evaluate the sphericity of the data before performing the ANOVA. In case the assumption of sphericity was violated, the degrees of freedom were corrected using Greenhouse-Geisser estimates of sphericity. To investigate the associations between changes in brain activity/connectivity and task performance changes, we will employ the Pearson correlation test. This test will help identify potential relationships between changes in brain activity and task performance, providing valuable insights into the neural mechanisms underlying our observations. All statistical analyses will be conducted using R [45].

We will preprocess rs-fMRI data using the fMRIPrep Pipeline [46] and analyze functional connectivity with the FSL software [47]. Our preprocessing steps encompass standard procedures, including slice-timing correction for synchronization across slices, realignment for motion correction, unwarping, spatial normalization, and smoothing via Gaussian kernel application. Additionally, we employ Nuisance Regression, which involves regressing out signals originating from non-neural sources such as white matter, cerebrospinal fluid (CSF), and global signal [48–50]. These strategies aim to mitigate confounding factors and enhance the reliability of our findings. Our analysis specifically targets the DLPFC due to its direct stimulation by tDCS, and will extend to the Default Mode, Salience, and Executive Control Networks, which are crucial for understanding schizophrenia’s cognitive aspects. We will employ seed-based correlations and ICA to identify coherent functional networks, ensuring a comprehensive exploration of brain connectivity. Multiple imputation will be the primary analysis strategy for addressing missing data (with the presence of more than 5% missing data) by employing fully conditional specification and predictive mean matching to generate ten imputed datasets. These imputed datasets will be used for the main analysis. The analysis will be conducted on each imputed dataset, and results will be combined following Rubin’s rules to provide comprehensive estimates and standard errors that account for missing data uncertainty. Sensitivity analyses will be performed to assess the impact of different missing data assumptions, ensuring the transparency and robustness of our findings. Any subtle and mild adverse effects will be reported using a checklist.

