**Methods:**

The study is designed as a randomized, double-blind, 2-arm parallel-group, sham-controlled, trial. Forty-eight participants with SCZ and cognitive impairment (measured via a set of executive functions tests) will be randomly allocated to receive either a single session of active (n = 24) or sham (n = 24) tDCS (20-min, 3-mA). The anodal and cathodal electrodes are positioned over the left and right DLPFC respectively. The stimulation occurs concurrently with the working memory task, which is initiated precisely 5 minutes after the onset of tDCS. Structural and resting-state (rs-fMRI) scans are conducted immediately before and after both active and sham tDCS using a 3 Tesla scanner (Siemens Prisma model) equipped with a 64-channel head coil. The primary outcome will be changes in brain activation (measures vis BOLD response) and working memory performance (accuracy, reaction time).

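### The efficacy ANOVA treats the pre-stimulation score as an outcome and names no decisive effect; baseline adjustment is more efficient, and the group main effect halves a true difference

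*Protocol article*

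**What the plan says.** Section 2.12 plans a mixed ANOVA on the three n-back indices (accuracy, d-prime and reaction time), set up "with time (before and after tDCS) as the within-subject factor and group (active tDCS and sham tDCS) as the between-group factor". The score taken before stimulation is therefore one level of the dependent variable, and no baseline covariate is mentioned. The same section then says that "The group × time interaction effect and the main effect of group and time will be explored", in order to judge whether changes in working memory and brain activation depend on stimulation type and time. None of the three effects is named as the one that decides.

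Section 2.5 sizes the trial on a different layout. It finds that "a minimum of 42 subjects is required to achieve 95% power at a significance level of 0.05" for a mixed ANOVA "with two groups, 3 measurements of working memory performance (baseline, during stimulation and 24 hours after stimulation", and then adds three patients per arm to reach 48. Section 2.10.2 defines the n-back primary outcomes as change from baseline to the online session and to 24 hours. Section 2.1 places the baseline n-back at least one week before the intervention session.

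**The concern.** Three effects are put forward for one efficacy question, and they do not answer the same question.

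- **Interaction.** With two time levels this is the between-arm comparison of mean change. It answers the right question, but it subtracts the baseline score in full instead of weighting it by how well it predicts the later score.
- **Group main effect.** This compares the arms on the average of a score that stimulation cannot have affected and a score that it can. A true effect is diluted by half, and half of any chance baseline difference is carried into the result.
- **Time main effect.** This pools the arms. Practice on a repeated n-back could produce it with no stimulation effect.

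The baseline score is already collected and could be used better. Without a named decisive effect, a report could rest on a term that is diluted or that does not compare the arms.

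**Working it through.** **Inputs.** From Section 2.5: 42 evaluable patients, f = 0.25, alpha 0.05, three measurements. From the abstract: 1:1 allocation. From Section 2.12: two time levels. Assumed, because the article does not state it: rho, the correlation between repeated scores, shown over 0.3 to 0.7. Scores are in units of a common SD. The value f = 0.25 is taken as printed; the partial eta squared of 0.10 beside it does not match (0.25² / (1 + 0.25²) = 0.059), which is a separate matter.

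**1. The plan's own figure.** For the interaction with m measurements, the noncentrality is lambda = N·m·f² / (1 − rho), on m − 1 and (N − 2)(m − 1) degrees of freedom. With m = 3, N = 42 and rho = 0.5, lambda = 42 × 3 × 0.0625 / 0.5 = 15.75 on 2 and 80 df, and power is 94.6%. The stated 42 is reproduced within rounding (43 patients, or 44 with equal arms, pass 95%). Rho of 0.3 would give 84.7% and 0.7 would give 99.7%, so only a value near 0.5 returns 42.

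**2. The two-level interaction of Section 2.12.** With two levels, a between-arm difference in change of D has interaction cell effects of ±D/4, so f = 0.25 means D = 4 × 0.25 = 1.0 SD. The change score has variance 2(1 − rho), and lambda = D²·N / (4 × 2(1 − rho)) on 1 and 40 df. At rho = 0.5, lambda = 42/4 = 10.5 and power is 88.5%.

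**3. Baseline adjustment on the same data.** The residual variance is 1 − rho². Its ratio to the change-score variance is (1 − rho²) / (2(1 − rho)) = (1 + rho)/2, that is 0.65, 0.75 and 0.85 at rho 0.3, 0.5 and 0.7. To allow for chance baseline imbalance the variance is multiplied by 1 + 1/(N − 4), and the test has N − 3 = 39 df. At rho = 0.5 and D = 1.0, lambda = 42 / (4 × 0.75 × 1.0263) = 13.64 and power is 95.0%; simulation of 40,000 trials also gave 95.0%.

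**4. Group main effect.** It estimates D/2 from subject means with variance (1 + rho)/2. For D = 1.0, lambda = 0.25 × 42 / (4 × (1 + rho)/2) = 4.04, 3.50 and 3.09 at rho 0.3, 0.5 and 0.7. Its type I error stays at about 5%.

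**Results at N = 42**

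| Assumed rho | Change score, 1.0 SD | Baseline-adjusted, 1.0 SD | Group main effect, 1.0 SD | Change score, 0.5 SD | Baseline-adjusted, 0.5 SD |
|---|---|---|---|---|---|
| 0.3 | 76% | 90.5% | 50% | 27% | 37% |
| 0.5 | 88.5% | 95.0% | 45% | 35% | 44% |
| 0.7 | 98.3% | 99.2% | 40% | 53% | 59% |

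If all 48 patients are evaluable, the 1.0 SD figures at rho = 0.5 are 92.4% and 97.2%.

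**The case against.** The strongest reply is that the interaction is a valid, unbiased test in a randomised trial, matches outcomes defined as change from baseline, and is listed first. Reporting every ANOVA term is routine, and the verb used is weak. Covariate adjustment is also often left to an analysis plan. Much of this stands: the issue is efficiency and a missing decision rule, not a biased primary test. But the article does fix the model and the list of effects, and it does so for the efficacy question, so this is a stated choice and not an omission.

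Three stronger readings are tempting and are not supported.

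- **That adjustment recovers a lost 95%.** The three-measurement ANOVA of Section 2.5 also treats baseline as an outcome level, and it has 94.6% at rho 0.5. The 88.5% arises because Section 2.12 has two levels where Section 2.5 has three. Section 2.12 also plans a sphericity test and correction, which have no role with two levels, so a three-level model may be intended. Against that model, for a 1.0 SD effect present online only and rho 0.5, power is 91.8%, and the gain from adjustment is about 3 points instead of 6.5.
- **That the ANOVA cannot be pooled after imputation.** The plan says that "results will be combined following Rubin’s rules". The two-level interaction is a single contrast with an estimate and a standard error, so pooling works directly.
- **That the group main effect inflates false positives.** It does not; the fault is dilution.

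**Conclusion.** The point holds as one of efficiency and of an unnamed decisive effect. Against the two-level analysis in Section 2.12, baseline adjustment gains about 14, 6.5 and 1 percentage points of power at rho 0.3, 0.5 and 0.7, for a 1.0 SD difference with 42 patients. For 0.5 SD the gain is about 6 to 10 points, but neither analysis exceeds 59%. The advantage disappears as rho approaches 1. The group main effect estimates half of a true difference and has 40 to 50% power where the interaction has 76 to 98%. The time effect says nothing about the arms.

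These figures rest on assumed values of rho, equal variances and two time levels. The change is worth making, but the planned interaction test would not be invalid without it.

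**What to change.** In Section 2.12:

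- For each n-back index, model the post-baseline values on arm with the baseline score as covariate. If both the online and the 24-hour tests are kept, as Section 2.10.2 has them, use a mixed model over the two occasions with arm × occasion.
- Report the arm difference at each post-baseline occasion with its 95% confidence interval, and name in advance which occasion is decisive. Do not average the two occasions for the decisive test: if the effect is present online only, the average has about 65% power at N = 42 and rho 0.5 (for the 1.06 SD online difference that f = 0.25 implies with three levels).
- For each ROI connectivity value, model the post-stimulation value on arm and the pre-stimulation value. The resting-state scans have no online occasion.
- State that the main effects of group and time are not evidence of efficacy.
- State the assumed rho and show power over a range of it, and make the number of time points agree between Sections 2.5 and 2.12.

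The cost is a change of wording, a standard model in R, one degree of freedom and the assumption of a roughly linear baseline relation. No further patients or measurements are needed.
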